##### Phase 1 analysis plan

Following grounded theory analyses [52], key points with similar themes will be grouped together into a category if mentioned several times by the CPs (e.g., Learning to communicate my concerns was helpful) [53]. Two staff members will then discuss each of the categories and generate underlying themes from the data (e.g., Sharing my worries with my partner drew us closer). After themes are extracted, content analysis will be used to identify quotations that fit each of the themes [54,55]. Then, we will independently sort quotations by theme and reach a consensus on any discrepancies. This analysis will be performed to understand both the feasibility and acceptability of the WBI for a CP population and to inform the delivery of the WBI in Phase 2.

#### Phase 2

Participants (N = 100) will be recruited as in Phase 1 from multiple Facebook FRG group pages. CPs will be randomly assigned to WBI or to the delayed-WBI after completion of their baseline survey, using computerized permuted block randomization with random size blocks, thereby ensuring the number of people allocated to each group is approximately equal throughout recruitment [56].

Table 2 displays our assessment measures. Data will be collected from CPs at baseline, after each WBI session, and 3 months after the fourth WBI session (or 4 months post-baseline for those who do not complete the WBI or who are in the delayed-WBI condition). Research staff will also schedule the WBI sessions with CPs during the consent process, asking them to complete one session every 10 days. Staff will monitor all participants through an online dashboard that tracks when surveys (and WBI sessions) are accessed and completed. If a CP has not completed a survey or session, staff will send e-mail reminders to complete the session and will follow up with phone calls as needed.

**Table 2 T2:** Baseline and 3-month follow-up assessment measures completed by CP

**Measure**	**Baseline**	**3 months**
Demographic information^1^	X	
CP concern about service member’s drinking^2^	X	X
Perceptions of service member alcohol use^2^	X	X
Service member’s perceived readiness to change drinking behavior and/or seek help^2^	X	X
Relationship quality^2^	X	X
Amount and quality of communication with service member about drinking^2^	X	X
CP’s behaviors around service member’s drinking (e.g., encouraging, enabling)^3^	X	X
Family conflict and cohesiveness^2^	X	X
CP alcohol use^3^	X	X
CP depressive symptoms^3^	X	X
CP anxiety symtpoms^3^	X	X
CP mental health service use^3^	X	X
CP general health and well-being^3^	X	X
WBI session usability measures^3^	X	X
Relationship communication style^1^	X	X

^1^ = covariate, ^2^ = primary outcome, ^3^ = secondary outcome.

Partners randomized to the delayed-WBI condition will be invited to complete the same WBI program after they complete their 3-month follow-up. This allows for all CPs to receive the WBI information after their study assessments have been completed. We will not assess outcomes in the delayed-WBI because this extends beyond the scope and budget of this pilot study. While the WBI is unproven for this population, the concepts are evidence-based from CRAFT and have been shown to be helpful to CPs [19-21]. Because participants report concern about their loved ones’ drinking, we feel it is important to provide them with the intervention information should they elect to receive it.

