In the current randomized controlled pilot study, *Partners Connect*, we will adapt CRAFT as a WBI for CPs living with service members who have alcohol misuse problems and evaluate the WBI compared to delayed-WBI at 3-month follow-up. Based on feedback from this study, we will develop a follow-on WBI module for use by the service members themselves. We will utilize the evidence-based CRAFT approach to serve as a model for intervention content, and the WBI will consist of four modules designed to be completed at the CP’s own pace. This study represents the first WBI for concerned military partners that targets service member alcohol misuse. It is self-sustainable and flexible, and thus expected to extend the reach and impact of existing preventive interventions. This study will fill an important gap in the alcohol misuse prevention literature and also help establish evidence that service members are willing to seek care and reduce drinking when their CPs are given resources to help them.

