##### Phase 2 analysis plan

Analyses will use the standard intent-to-treat (ITT) approach to examine the effect of offering the WBI to all CPs. Our ITT approach will analyze CPs as belonging to the group they were randomized to, regardless of their compliance, because excluding CPs that do not complete their WBI sessions would bias our results in favor of the WBI and increase the type I, or false positive, error rate [57].

Our proposed primary outcomes will be to examine if CPs report fewer concerns about their partner’s drinking [58] and measure perceived reductions in their partner’s drinking [59], perceived increases in their partner’s readiness to change or seek help, and perceived improvement in relationship and communication quality [58,60,61]. These measures will be beta-tested in Phase 1 (see Table 2).

The data will be analyzed with an aim of providing information to improve the planning of a larger trial. We will examine the distributions of variables and consider the implications for refining these measures (e.g., to eliminate floor and ceiling effects). Our primary analysis will be to examine differences in outcomes between WBI and the delayed-WBI group 3 months after the intervention. For continuous outcomes, we will use the SAS PROC MIXED procedure to analyze changes in outcome variables from baseline to follow-up. PROC MIXED is a robust procedure used to determine missing values and correlations between outcome variables, so it has been recommended for the analysis of ITT designs [62]. For categorical outcomes, we will use the SAS PROC GLIMMIX procedure, which estimates mixed models with binomial outcomes. If the sample is demographically diverse (by age, race/ethnicity), then we will control for these characteristics.

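### Follow-up is timed from session 4 for WBI completers and from baseline for everyone else, so the arms are assessed at the same time since randomization only if session 4 falls about 30 days after baseline

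*Protocol article*

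**What the plan says.** All of this is in the Protocol article, under Methods/design unless stated otherwise.

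- **Start of the clock.** Procedures, Phase 2: "CPs will be randomly assigned to WBI or to the delayed-WBI after completion of their baseline survey". Baseline and randomization are therefore close to the same date.
- **Follow-up date, WBI completers.** Same section: "3 months after the fourth WBI session (or 4 months post-baseline for those who do not complete the WBI". The opening words set the date for completers; the parenthesis begins the exception.
- **Follow-up date, everyone else.** Same sentence, the exception in full: "4 months post-baseline for those who do not complete the WBI or who are in the delayed-WBI condition".
- **Pace.** Staff schedule the WBI sessions with CPs during consent, "asking them to complete one session every 10 days". Staff watch a dashboard, send e-mail reminders and telephone when a session is overdue. The Background describes the program as self-paced: "the WBI will consist of four modules designed to be completed at" the CP's own pace.
- **Primary comparison.** Phase 2 analysis plan: "Our primary analysis will be to examine differences in outcomes between WBI and the delayed-WBI group 3 months after the intervention".
- **Analysis principle.** Same section: "Our ITT approach will analyze CPs as belonging to the group they were randomized to, regardless of their compliance". The stated aim is the effect of offering the WBI.

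**The concern.** Two different events start the follow-up clock, and one of them can occur only in the WBI arm. Within that arm, whether and when a CP finishes session 4 decides when she is assessed. In the delayed-WBI arm the date is fixed. The primary comparison is defined by time since the intervention, which has no direct meaning for CPs who have not yet been offered it. The 4-month rule stands in for it, and it is equivalent only if session 4 is completed about one month after baseline.

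This matters if the outcomes move with time since enrollment regardless of treatment. CPs must think their partner has a drinking problem in order to enter, so some regression toward the mean in reported concern and drinking is plausible. If WBI completers are seen later than controls, that movement is credited to the WBI. If they are seen earlier, it counts against it. Randomization does not protect against this, because the gap arises afterwards and depends on compliance.

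Adjusting for elapsed time would not be a reliable repair. By schedule the controls are all seen at one time and so carry no information on drift at other times. Elapsed time among WBI CPs is mixed up with how they used the program.

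**Working it through.** **Inputs from the article.** Four sessions; requested spacing 10 days; completers assessed 3 months after session 4; all others assessed 4 months after baseline; 50 CPs per arm.

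**Conventions and assumptions.** One month = 365.25/12 = 30.44 days, so 3 months = 91.3 days and 4 months = 121.8 days. Session 1 on day 0 is an assumption for Phase 2; it follows the Phase 1 default of going straight from the baseline survey to session 1. Other start days and spacings are illustrations.

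**Step 1: the plan's own alignment.**

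Completer follow-up day = start day + 3 × spacing + 91.3. All others: day 121.8.

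On schedule: 0 + 3 × 10 + 91.3 = 121.3. The difference is -0.4 days before rounding, so the 4-month figure reproduces as a match to 3 months after session 4.

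**Step 2: departures from schedule.**

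| Session 1 on day | Spacing (days) | Session 4 on day | Follow-up day | Difference from controls (days) |
|---|---|---|---|---|
| 0 | 2 | 6 | 97.3 | -24 |
| 0 | 10 | 30 | 121.3 | 0 |
| 10 | 10 | 40 | 131.3 | +10 |
| 0 | 14 | 42 | 133.3 | +12 |
| 0 | 21 | 63 | 154.3 | +33 |

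The 14-day row is the upper end of the spacing that the article calls ideal in Phase 1.

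**Step 3: shift in the arm mean.** Non-completers share the controls' date, so with completion share c and a day-0 start the mean lag is c × (3 × spacing - 30.44). With c = 70% (assumed):

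- 10-day spacing: 0.7 × (30 - 30.44) = -0.3 days
- 14-day spacing: 0.7 × (42 - 30.44) = +8 days
- 21-day spacing: 0.7 × (63 - 30.44) = +23 days

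With c = 100% and 14-day spacing the lag is +12 days.

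**Step 4: what a lag could do to the test.** Assume drift of 0.1 SD per month and a baseline-to-follow-up correlation of 0.5. The standard error of the baseline-adjusted difference is then √[(2/50) × (1 - 0.5²)] = √0.03 = 0.173 SD. Spurious effect = 0.1 × lag/30.44. With z = spurious effect/0.173, the two-sided 5% test rejects with probability P(Z > 1.96 - z) + P(Z < -1.96 - z).

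| Mean lag | Spurious effect (SD) | z | Type I error |
|---|---|---|---|
| 8 days | 0.026 | 0.15 | 5.3% |
| 12 days | 0.039 | 0.23 | 5.6% |
| 23 days | 0.075 | 0.43 | 7.2% |
| 1 month | 0.100 | 0.58 | 8.9% |

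**Step 5: what a one-month mean lag requires.** Setting c × (3 × spacing - 30.44) = 30.44 gives a spacing of about 25 days at 70% completion and about 20 days at 100%. That is two to two and a half times the requested pace.

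**The case against.** The strongest reply is that the 4-month figure was evidently chosen to line up the arms, and at the requested pace it does so to within a day. The plan also works to keep CPs on schedule, with sessions booked at consent, a dashboard, reminders and calls. This stands. It makes long lags less plausible, though it does not remove late starts or uneven pace in a self-guided program.

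A reader might infer that the two arms are in fact measured at different times since randomization. The documents do not support that. They set a rule under which the times differ if pace departs from plan, in either direction.

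A reader might also infer that intention-to-treat is breached. It is not: non-completers are followed up and analyzed as randomized. The narrower point remains that compliance sets the assessment date.

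The absence of a latest date for session 4 or a visit window should not be held against the article, since such details commonly sit in a full protocol or SAP. A window or cut-off there would limit the mismatch but would leave two clocks.

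Finally, a single clock changes the question for slow completers, because the stated target is 3 months after the intervention. That is a genuine trade-off. It favors the single clock here because the declared aim is the effect of offering the WBI, and for CPs in the delayed arm time since the intervention is undefined.

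**Conclusion.** The point holds as a conditional weakness in the visit schedule. The two clocks coincide only when session 4 falls about 30 days after baseline. Otherwise WBI completers are assessed at a different time since randomization from controls, by an amount that depends on their own compliance.

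The size of any bias cannot be stated from the documents, and its direction is unknown. The illustrations rest on assumed spacing, start day, completion, drift and correlation. Under them, mean lags of 8 to 12 days move type I error only from 5% to about 5.3% to 5.6%. The figure of about 9% needs a one-month mean lag, which nothing in the article supports, and should not be read as the expected effect.

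This is a pilot meant to inform a larger trial. The point is therefore a cheap improvement worth making, also so that the two-clock rule is not carried forward, and not a flaw that must be fixed before the trial can proceed.

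**What to change.** Schedule every CP's follow-up at 4 months post-randomization in both arms, with one common window, whatever number of sessions was completed. Reword the primary comparison in the Phase 2 analysis plan as the difference between arms at 4 months post-randomization, and bring the 3-month labels elsewhere in the article into line. Record time since last session and report it descriptively, in the WBI arm only.

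The scheduled difference between arms then becomes 0 days at any pace, and a completer exactly on schedule moves by less than one day (121.3 to 121.8).

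The cost is wording and one scheduling setting, with no extra visit. The price is a shorter interval since session 4 for slow completers: 121.8 - 42 = about 80 days at 14-day spacing and 121.8 - 63 = about 59 days at 21-day spacing, instead of 91.

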##### Phase 2 analysis plan

Analyses will use the standard intent-to-treat (ITT) approach to examine the effect of offering the WBI to all CPs. Our ITT approach will analyze CPs as belonging to the group they were randomized to, regardless of their compliance, because excluding CPs that do not complete their WBI sessions would bias our results in favor of the WBI and increase the type I, or false positive, error rate [57].

Our proposed primary outcomes will be to examine if CPs report fewer concerns about their partner’s drinking [58] and measure perceived reductions in their partner’s drinking [59], perceived increases in their partner’s readiness to change or seek help, and perceived improvement in relationship and communication quality [58,60,61]. These measures will be beta-tested in Phase 1 (see Table 2).

The data will be analyzed with an aim of providing information to improve the planning of a larger trial. We will examine the distributions of variables and consider the implications for refining these measures (e.g., to eliminate floor and ceiling effects). Our primary analysis will be to examine differences in outcomes between WBI and the delayed-WBI group 3 months after the intervention. For continuous outcomes, we will use the SAS PROC MIXED procedure to analyze changes in outcome variables from baseline to follow-up. PROC MIXED is a robust procedure used to determine missing values and correlations between outcome variables, so it has been recommended for the analysis of ITT designs [62]. For categorical outcomes, we will use the SAS PROC GLIMMIX procedure, which estimates mixed models with binomial outcomes. If the sample is demographically diverse (by age, race/ethnicity), then we will control for these characteristics.

We will also carry out an exploratory analysis to see if changes in alcohol use are accompanied by changes in CP reports of relationship satisfaction. Previous research has established that alcohol misuse is correlated with relationship dissatisfaction [63], but this analysis will demonstrate whether a decrease in alcohol use by the service member is associated with increases in relationship satisfaction compared to baseline. We will also explore relationship satisfaction, CP alcohol consumption, and couples communication style as moderators of the effectiveness of the CP’s WBI. Separate models will be utilized to assess changes in perceptions of service members’ alcohol use as the product of the intervention condition and each moderating variable. Specifically, we will enter the interaction of each of these variables with intervention condition into separate mixed models for predicting pre/post changes in perceived service member alcohol use. Such analyses are underpowered for conventional hypothesis tests and would therefore be preliminary.

#### Phase 3

The goals of Phase 3 are twofold: 1) to gather feedback on how service members responded to their partners completing our WBI; and 2) to assess whether service members would be receptive to completing a WBI module or other intervention tailored to their drinking. Including a service member component in this study is essential to understanding the impact of the CP-focused WBI. This information can also elucidate CP outcomes (e.g., if we find that CPs reported improved communication with their partner regarding drinking, we can corroborate this information with service members). In addition, if we find that service members reacted negatively to their CP receiving the WBI, this would be helpful information to inform future iterations of the CP-focused WBI. Finally, anything service members found helpful from their CP attending the WBI may also be used to inform future development of a service member-focused WBI. For example, we will provide examples of a service member-focused WBI and if the service members provide feedback to us that it is too lengthy or burdensome, we would use this knowledge to help restructure the service member WBI accordingly.

While the construction of the add-on service member intervention module would be out of scope and budget for the current study, the results of this phase would directly prepare us for a future trial that evaluates a larger randomized controlled study of a WBI for CPs with a follow-on intervention for service members.

During phone interviews (~30 minutes) with the service members, we will assess the impact of the WBI on the service member (e.g., What do you know about the web program your partner completed? What differences, if any, did you notice in your partner? What do you think about those differences?). We also will assess how receptive they are to completing a WBI tailored specifically for them (e.g., There are a few options for help-seeking I’d like to discuss with you. If a confidential web program was made available to you, what’s the likelihood you would check it out? What factors would make it more likely that you would check it out [e.g., confidential, not tied to military reporting]? What factors would make it more difficult? What types of information would you want to know about? What types of information would “turn you off?” May I describe a couple of examples to get your feedback on how these can be improved?).

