**Methods/design:**

The WBI will be adapted from the Community Reinforcement and Family Training (CRAFT) intervention. In the first phase, we will develop and beta-test the WBI with 15–20 CPs. In the second phase, we will randomize CPs to WBI (n = 50) or to delayed-WBI (n = 50) and evaluate the impact of the WBI on CPs’ perceptions of service member help-seeking and drinking, as well as the CP’s well-being and relationship satisfaction 3 months after the intervention. In the third phase, we will recruit 15–20 service members whose partners have completed the study. We will interview the service members to learn how the CP-focused WBI affected them and to assess whether they would be receptive to a follow-on WBI module to help them.

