### Recruitment

Participants in Phases 1 and 2 will be recruited through Facebook FRG pages in two ways. There currently are over 100 region-specific FRGs on Facebook, with between 30 and 500 members each. We will recruit CPs by: 1) asking FRG administrators for their permission to post study information on their Facebook page; and 2) posting advertisements for FRG Facebook members.

Facebook FRGs are private groups hosted on Facebook and maintained by family members themselves. Each official Facebook FRG page has an administrator (i.e., family member of a service member) that maintains the site, accepts other FRG members on Facebook into the group, posts announcements for events, and facilitates connections between other FRG members on the site. We will ask the administrators of these Facebook group pages to let group members know about an opportunity to participate in our study.

Facebook recruitment strategies such as these have successfully recruited large samples of military and civilian samples for research studies [40-43]. This type of recruitment method has also been successful in prior research with young adults and has the ability to recruit nationally representative samples for generally low cost [40,43]. Based on previous studies, we conservatively anticipate being able to recruit 100 participants in less than 3 months. For example, Brief et al. [41] recruited 600 participants in 6 weeks using Facebook recruitment methods only. Female CPs are estimated to make up the entire sample based on other studies recruited from FRGs [44]. CPs are estimated to be an average age of 27 and primarily Caucasian (66%), with smaller proportions of Hispanic (18%), African American (11%), Asian/Pacific Islander (3%), Native American (1%), and Other (1%) [44].

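### The continuous primary analysis is described as change from baseline without naming the baseline outcome as a covariate, and demographic adjustment hangs on an undefined diversity trigger: an avoidable loss of precision, not a bias

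*Protocol article*

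**What the plan says.** The article's Phase 2 analysis plan sets the primary contrast: "Our primary analysis will be to examine differences in outcomes between WBI and the delayed-WBI group 3 months after the intervention". For continuous outcomes the model is stated as "we will use the SAS PROC MIXED procedure to analyze changes in outcome variables from baseline to follow-up", and PROC MIXED is justified by its handling of missing values and correlated outcomes. The text does not say whether the response is a change score, whether baseline is a repeated response, or whether baseline means are constrained. The later moderator paragraph again describes mixed models for pre/post change.

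On covariates the plan says: "If the sample is demographically diverse (by age, race/ethnicity), then we will control for these characteristics". No criterion for diversity follows. Table 2 labels demographic information and relationship communication style as covariates. It labels the other measures as primary or secondary outcomes, and the primary outcomes are collected at both baseline and 3 months. On timing, the Phase 2 procedures state: "CPs will be randomly assigned to WBI or to the delayed-WBI after completion of their baseline survey". The planned size is 50 per arm. No correlation, standard deviation, effect size, alpha or power is given.

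**The concern.** Each primary outcome has one baseline and one follow-up measurement, and randomization makes the expected baseline means equal. An analysis of change that leaves baseline means free does not use that fact: it subtracts the whole baseline value, noise included, where a regression would subtract only the predictive part. When baseline predicts follow-up weakly, subtraction adds more noise than it removes. With 50 per arm, and estimates meant to inform a larger trial, precision that costs nothing is worth taking.

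The covariate rule is a separate weakness. Without a threshold, the primary model is settled by a judgement about how the sample looks, and spread in age or ethnicity is not the same as prognostic value. That leaves open which version of the analysis is the primary one.

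**Working it through.** **Inputs.** From the document: n = 50 per arm, one baseline and one follow-up, baseline completed before randomization. Assumed, because the document does not state them: rho from 0.3 to 0.7 (0 to 0.9 also shown), equal standard deviations (set to 1), complete data. The plan states no figure that could be reproduced first.

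**Variance of the treatment contrast**, as a multiple of 2/n:
- Change score: 2(1 − rho)
- Follow-up only: 1
- ANCOVA: 1 − rho²

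The ratio of ANCOVA to change score is (1 − rho²)/[2(1 − rho)] = (1 + rho)/2, so the share of variance removed is (1 − rho)/2.

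| rho | Change score | ANCOVA | Variance removed |
|---|---|---|---|
| 0 | 2.00 | 1.00 | 50% |
| 0.3 | 1.40 | 0.91 | 35% |
| 0.5 | 1.00 | 0.75 | 25% |
| 0.7 | 0.60 | 0.51 | 15% |
| 0.9 | 0.20 | 0.19 | 5% |

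Below rho 0.5 the change-score variance exceeds 1, so it is less precise than ignoring baseline altogether.

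**Simulation.** With 20,000 trials of 50 per arm, the reductions were 34.9%, 24.4% and 14.7% at rho 0.3, 0.5 and 0.7, in line with the formula.

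**Does PROC MIXED alter this?** With both time points as responses and known covariance, generalized least squares gives:
- Group-by-time term with free baseline means: 1.40, 1.00 and 0.60 at rho 0.3, 0.5 and 0.7, the same as the change score.
- Baseline means constrained equal: 0.91, 0.75 and 0.51, the same as ANCOVA.

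Modelling change with baseline as a covariate also reproduces ANCOVA. So the loss depends on the specification, not on the procedure.

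**Scale.** At rho 0.5 with 50 per arm, the variance is (2/50) × 1.00 = 0.040 for change and (2/50) × 0.75 = 0.030 for ANCOVA. The gain is equivalent to 100/0.75 = 133 participants instead of 100. For illustration only, with an assumed effect of 0.5 SD and two-sided 0.05, power by the normal approximation rises from 56% to 75% (rho 0.3), from 70.5% to 82% (rho 0.5) and from 90% to 94% (rho 0.7). Noncentral-t values are about a point lower or equal.

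**Unequal standard deviations.** With s0 at baseline and s1 at follow-up, the change-score variance minus the ANCOVA variance is (s0² + s1² − 2·rho·s0·s1) − s1²(1 − rho²) = (s0 − rho·s1)². This is never negative. The percentages shift, but the direction does not.

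**The case against.** The strongest objection is that the sentence does not fix a model. It also fits PROC MIXED with constrained baseline means, or change regressed on baseline, and under either the loss is zero. A condensed article may leave that detail to the full plan. This stands as a limit on the claim: the loss is conditional on the reading. It does not remove the point, because the article does name its adjustment variables, and the baseline outcome is not among them.

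It is also fair that a change-score comparison is unbiased in a randomized trial, and that this is a pilot with no stated power target. The diversity trigger rests on demographics collected before randomization, not on outcomes. In a complete-data group-by-time model, demographic main effects leave the treatment estimate unchanged, so there the choice is harmless. That no longer holds once follow-up data are missing, or if the response is a change score or the follow-up value.

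Three stronger readings might be inferred, and the document does not support them:
- *That demographics are the only planned adjustment.* Table 2 also labels relationship communication style as a covariate.
- *That race/ethnicity cannot be estimated.* The Recruitment section projects two categories at 1% each. Such a category is missing from at least one arm with probability 1 − (1 − 0.99^50)² = 84%, but a main effect does not need members in both arms. Nor does the plan say that all six levels will enter the model.
- *That the variance gain covers every primary outcome.* Categorical outcomes go to PROC GLIMMIX, where the formula does not apply. Baseline adjustment of a logistic model also changes the odds ratio being estimated.

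**Conclusion.** The point holds as one of precision, for continuous outcomes. Read as a raw change score or as a group-by-time model with free baseline means, the planned analysis is valid but gives up (1 − rho)/2 of its variance relative to baseline adjustment: 35% to 15% if rho is 0.3 to 0.7, and 50% to 5% over rho 0 to 0.9. This assumes equal standard deviations and complete data. Rho is an assumption, so no single percentage is a property of this plan, and the loss is zero if the full plan already conditions on baseline.

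The undefined diversity trigger is a pre-specification weakness in its own right. It contributes nothing to the variance figure, and no bias from it has been shown.

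**What to change.** 1. State that each continuous follow-up outcome is modelled with arm and its own baseline value or, equivalently for precision, in PROC MIXED with both time points as responses and baseline means constrained equal across arms. If the full plan already does this, one sentence in the description is enough.
2. Replace the diversity condition with a small covariate set fixed before outcomes are seen and used whatever the sample looks like. Collapse sparse race/ethnicity levels by a rule written in advance, and say whether communication style, already labelled a covariate in Table 2, belongs to the set.

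The cost is two sentences and a changed model statement. No further data collection is needed, since the baseline values are already gathered before randomization.
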